### Follow-up assessments

Three months after admission, a home visit is made by a trained nurse, to perform a Mini-Mental State Examination (MMSE) [31] and to measure the grip-strength of the dominant hand. The MMSE is a validated 30-point questionnaire-based test that is used to screen for cognitive impairment. Twelve months after the hospital admission, the patient is visited again at home by a trained nurse to perform a MMSE test and a Katz ADL index score and to assess grip-strength. Additionally, the patient's primary caregiver is asked to complete the caregiver's version of the Katz ADL index score and the IQCODE-sf by telephone.

### Delirium treatment

All patients receive 'care as usual', which means that if postoperative delirium occurs, patients are treated according to standard procedures and assessed for delirium severity and duration. Any underlying illness is treated according to the hospital guidelines. If there is a clinical diagnosis of hyperactive or mixed delirium, treatment with anti-psychotics (most frequently with haloperidol) is started according to a fixed scheme. Daily adjustment of medication takes place depending on the clinical judgement of the consulting geriatric team and/or the attending physician. Antipsychotic medication is standardised as much as possible, with escape medication in cases of acute aggravation. Patients on psychiatric medication, apart from their delirium medication, can continue their prescriptions throughout the study-period because melatonin does not interfere with any other medication.

### Power analysis

The primary endpoint is the occurrence of delirium during the first eight days after the start of study medication. In the AMC, the incidence of delirium in patients after surgical repair of hip fracture is now over 50% [2]. The prevention of delirium has been previously assessed in several studies. At the time this study began, other studies using medication prophylaxis had not shown any significant reduction in the incidence of delirium. Assuming an absolute reduction of 13%, with a 50% incidence of delirium in the control group and an incidence of 37% in the intervention group, we require 226 patients per group (452 patients in total) to detect differences with a power of 80% and a two-sided alpha of 0.05.

### Statistics

Data will be primarily analysed according to the intention-to-treat principle and secondarily compared by per protocol analysis. To study the effectiveness of the melatonin treatment, the difference in the occurrence of delirium between patients treated with or without melatonin will be tested with Chi-square statistics. Continuous secondary outcome measures, if normally distributed, will be tested using a Students' t-test, otherwise Mann-Whitney tests will be employed. The duration of delirium will be tested using a log-rank test. Categorical outcome variables will be tested with a Chi-square test. Outcomes for patients who had delirium at day one of the study will be calculated separately. Subsequently, multivariable logistic regression will be used to compare differences between melatonin and placebo groups in the primary and in the secondary outcome measures.

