### Randomisation

A randomisation schedule, made by an independent statistician, is employed that is stratified by study centre and uses block randomisation of ten participants per block. The trial-pharmacist is the only one in possession of the randomisation list.

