### Data collection

Demographic data, medical history and medication use are recorded. Once included in the study, patients are visited daily (and once during the weekend) for efficacy and safety evaluations by an experienced team of geriatric nurses and geriatricians. For the diagnosis of delirium, the Cognitive Assessment Method (CAM) is used [22,23]. The CAM was developed in 1990 and is a validated and widely used screening tool for the presence of delirium. When patients are delirious, the severity of delirium is examined using the Delirium Rating Scale-Revised-1998 (DRS-R-98). The severity of delirium is expressed as the maximum DRS-R-98 score during the delirium period. Subtyping is examined using the Delirium Symptom Interview [24] and the Delirium Motoric Checklist [25]. Cognitive and functional status and the presence of impairment prior to admission are assessed. Each patient and their primary caregiver are asked to complete questionnaires to assess the patient's pre-existent functional and cognitive state two weeks prior to hospital admission. Functional status is assessed using the 15-item Katz Activities of Daily Living (ADL) index score, based on the situation two weeks prior to admission, to be completed by the patient or their closest relative in cases of cognitive impairment. Impairment is calculated using the number of impaired ADLs [26].

Primary caregivers are asked to complete the Informant Questionnaire on Cognitive Decline short form (IQCODE-sf) [27] by recalling the situation two weeks prior to the hip fracture and comparing this with the situation ten years earlier. Patients with a mean score of 3.9 or higher are considered to have global cognitive impairment [28]. Grip strength of the dominant hand, as an objective measurement of functional status [29], is measured using hand-held dynamometry. The severity and number of comorbidities is scored using the Charlson comorbidity index [30]. At the time of discharge from the hospital the total amount of haloperidol and other antipsychotics used during hospital admission is recorded, also the length of stay and in-hospital complications are collected.

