## Discussion

With an ageing population, older persons become a larger part of the hospital population. Experiencing delirium has major consequences for these patients' outcomes following hospital stay. From treatment trials with haloperidol, it became known that once delirium exists, it is difficult to influence its duration [32]. The prevention of delirium should therefore be a main focus in the treatment of older persons in hospital. To be able to adequately compare the placebo versus melatonin intervention, we selected an RCT-design. Because the proposed study is a prevention trial, the primary measure is 'occurrence of delirium'. We decided to enrol acutely admitted hip fracture patients because they represent a homogeneous group with a high incidence of delirium. To achieve good external validity, we include patients with dementia as well because they are especially prone to develop delirium. Therefore, the results will be widely applicable to the general older hospital population.

The proposed study will contribute to our knowledge because studies on the prophylactic treatment of delirium with follow up remain scarce. Our work may lead to a prophylactic treatment for frail older persons at high risk for delirium that is safe, effective, and easily implementable in daily practice.

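### The first-named primary test is an unadjusted chi-square; making the planned regression primary, with centre, age and pre-fracture cognition, would recover some power at little cost

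*Protocol article*

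**What the plan says.** The Statistics section of the protocol article gives the test of the primary outcome: "the difference in the occurrence of delirium between patients treated with or without melatonin will be tested with Chi-square statistics". It names no strata and no covariates. Later in the same section it adds: "Subsequently, multivariable logistic regression will be used to compare differences between melatonin and placebo groups in the primary and in the secondary outcome measures". The article does not say which of these two analyses carries the confirmatory conclusion.

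Three other sections bear on the choice:

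- Randomisation: the schedule is "stratified by study centre and uses block randomisation of ten participants per block".
- Data collection: demographic data are recorded, and the primary caregiver completes the IQCODE-sf about the state before the fracture. A cut-off is already fixed: "Patients with a mean score of 3.9 or higher are considered to have global cognitive impairment".
- Discussion: "we include patients with dementia as well because they are especially prone to develop delirium".

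The Power analysis section sizes the trial for a plain comparison of two proportions, "with a 50% incidence of delirium in the control group and an incidence of 37% in the intervention group", with 226 patients per group, "to detect differences with a power of 80% and a two-sided alpha of 0.05".

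**The concern.** The order of the analyses and the sample size calculation both suggest that the unadjusted test decides the trial. That test ignores the factor used to stratify the allocation. It also ignores the patient characteristic that the article itself singles out as raising the risk of delirium, although this characteristic is measured in any case.

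Two things are at stake. The first is power: for a binary outcome, adjusting for a prognostic baseline variable usually makes the test of treatment more powerful. The second is chance imbalance: if one arm happens to contain more cognitively impaired patients, the crude comparison moves with it. A further, smaller matter is that two analyses of the primary outcome without a stated order of authority leave room for doubt if they fall on different sides of 0.05.

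**Working it through.** **Inputs from the documents.** Control risk 0.50, melatonin risk 0.37, 226 per group, two-sided alpha 0.05, power 80% (Power analysis). Stratification by centre (Randomisation). IQCODE-sf cut-off 3.9 (Data collection). The documents give no prevalence of cognitive impairment, no odds ratio for it, no age effect and no delirium rates by centre, so all of these are assumed below.

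**Step 1: the plan's own figure.** The mean risk is (0.50 + 0.37)/2 = 0.435. With the pooled formula,

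n = [1.960 × √(2 × 0.435 × 0.565) + 0.842 × √(0.50 × 0.50 + 0.37 × 0.63)]² / 0.13²
= [1.374 + 0.585]² / 0.0169 = 227.1, so 228 per group.

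The unpooled formula gives 225 and the arcsine formula 227. The stated 226 is reproduced. Power at 226 per group is

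Φ[(0.13 − 1.960 × √(0.49155/226)) / √(0.4831/226)] = Φ(0.0386/0.0462) = Φ(0.835) = 79.8%.

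The chi-square therefore gives the power the trial was planned for.

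**Step 2: adjusting for a baseline predictor.** Trials were simulated with 226 per arm and the marginal risks held at 50% and 37%. The chi-square was compared with a logistic regression on arm and one predictor (4,000 runs per scenario, Monte Carlo standard error about 0.6 points).

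| Assumed predictor | Chi-square | Adjusted | Gain (points) |
|---|---|---|---|
| No prognostic value | 80.6% | 80.2% | −0.4 |
| Binary, 40% prevalence, OR 2 | 81.9% | 82.1% | 0.2 |
| Binary, 40% prevalence, OR 3 | 79.9% | 82.5% | 2.6 |
| Binary, 40% prevalence, OR 5 | 79.9% | 85.8% | 5.9 |
| Continuous, AUC 0.63 | 81.4% | 83.2% | 1.8 |
| Continuous, AUC 0.74 | 80.0% | 86.2% | 6.2 |

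A second set (3,000 runs per scenario) used centre-stratified allocation and a model with centre, age and IQCODE class. It assumed impairment in 30% to 35% with OR 3 to 6, age OR 1.3 to 1.6 per SD, and centre OR 1.0 to 2.5. Chi-square against adjusted power was 78.8/81.8, 81.2/85.3, 80.5/86.0, 81.1/88.5 and 81.7/84.3, which are gains of 3.0, 4.1, 5.5, 7.4 and 2.6 points. With OR 5 and 20% of IQCODE scores missing, the gain falls to about 4 points.

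**Step 3: the same gain in patients.** The required size scales with (1.960 + z_power)². Going from 79.9% (z = 0.838) to 82.5% (z = 0.935) is worth (2.895/2.798)² = 1.07, or about 30 patients on 452. Going to 85.8% (z = 1.071) is worth (3.031/2.798)² = 1.17, or about 80 patients.

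**Step 4: centre alone.** A centre-stratified Mantel-Haenszel test was compared with the chi-square, assuming two equal centres (200,000 runs).

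| Assumed control rates | Chi-square | Stratified | Type I error: chi-square | Type I error: stratified |
|---|---|---|---|---|
| 50% / 50% | 80.3% | 80.3% | 5.3% | 5.3% |
| 55% / 45% | 80.2% | 80.3% | 5.2% | 5.2% |
| 60% / 40% | 80.6% | 80.9% | 4.9% | 5.0% |
| 65% / 35% | 81.4% | 83.5% | 4.4% | 5.1% |

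Centre adds 0 to 0.4 points, and about 2 points only when the rates differ as widely as 65% and 35%. When centres differ, ignoring centre makes the test conservative.

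**Step 5: chance imbalance.** At an assumed 40% prevalence, the standard error of the between-arm difference in prevalence is √(2 × 0.40 × 0.60/226) = 4.6 points, so 95% limits are about ±9 points. With OR 3 to 5 at an overall risk of 50%, the risk gap between impaired and unimpaired patients is about 27 to 38 points. The crude risk difference can then shift by about 0.09 × 27 = 2.4 to 0.09 × 38 = 3.4 points, against a target of 13.

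**Step 6: what adjustment costs if the covariates are useless.** Power was 80.2% with one useless covariate and 79.7% with three more, against 80.6% for the chi-square. Averaged over eight null scenarios of 2,000 runs each, type I error was 5.1% adjusted and 5.6% for the chi-square (standard error about 0.2 points).

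**The case against.** The strongest reply is that nothing here is wrong. The trial was sized for a two-proportion test and uses one. The test holds its error rate and delivers the planned power. Adjustment is already planned, so the disagreement is only over which analysis comes first. The covariate list of the regression may properly sit in an analysis plan or full protocol that is not shown, so its absence from the article is no fault. All of this stands.

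It is also fair that the size of the gain rests on assumptions. The article says in words that patients with dementia are prone to delirium but gives no odds ratio, and it calls the hip fracture population homogeneous. The Background says that most patients with delirium have prior cognitive impairment. If that held here at a 50% incidence, the odds ratio would exceed (0.25/0.25)/(0.15/0.35) = 2.3 at 40% prevalence and (0.25/0.25)/(0.10/0.40) = 4 at 35%. But the statement is general and the prevalence is not given; at 50% prevalence the same bound is only 1. It makes a moderate predictor plausible and proves nothing about this trial.

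A third objection concerns the covariate. The IQCODE-sf is caregiver recall, and the article does not say that it is completed before the first dose or before delirium appears. This stands and has to be part of the fix.

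The reply does not remove the point. Choosing the less efficient test as the first one is a stated choice, and the data for a better one are already collected.

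**Conclusion.** The point holds as a cheap improvement in efficiency. Under assumed odds ratios of 2 to 6 for cognitive impairment, an adjusted primary analysis gains about 0 to 7 points of power. The gain is near zero at an odds ratio of 2, about 2.6 to 6 points at 3 to 5, and smaller with missing IQCODE scores. If the covariates carry no information, the loss is under 1 point. Nearly all of the gain comes from cognition and age.

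Three stronger readings are tempting, and the documents do not support them:

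- A reader might infer that ignoring the stratification factor invalidates the test. It does not: type I error stayed near 5% and fell when centres differed.
- A reader might infer that the trial is underpowered by its choice of test. The formula gives 79.8% and the simulations about 79% to 82%, which is what was planned.
- A reader might infer that the plan neglects baseline factors or that adjustment would cure imbalance. The regression is planned, only in second place. Adjustment for a dichotomised score with some values missing reduces the effect of imbalance in measured factors but does not remove it.

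**What to change.** By a dated amendment before unblinding, since the trial is in progress:

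- State that the primary analysis is the already planned logistic regression of delirium on arm, limited to centre, age and pre-fracture cognitive impairment (IQCODE-sf 3.9 or higher, lower, or no score as a separate category).
- Require that the IQCODE-sf refers to the state before the fracture and, where possible, is obtained before delirium status is known.
- Exclude factors that arise after randomisation. The Study design section lists peri- and postoperative complications among possible confounders; the article does not say they enter the model, but the amendment should rule it out.
- Report the effect as a standardised risk difference with 95% CI. This keeps the result on the scale of the 13-point target, whereas the odds ratio changes with the covariates: in the simulations the log odds ratio for arm was −0.53 with no predictor and −0.62 with a binary predictor of OR 5, for the same 50% and 37%.
- Keep the chi-square as a supporting analysis.

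The cost is a short amendment and a rule for missing IQCODE scores. No new data and no change in sample size are needed.

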### Study population and recruitment

The study population consists of patients of 65 years and older who are admitted for the surgical treatment of hip fractures. Hip fractures are defined as fractures of the femoral neck, the trochanteric region or the proximal femur. Further inclusion criteria are enrolment within 24 hours of admission and the patient must be willing and medically able to receive the study medication according to the protocol for the duration of the study. Exclusion criteria are the inability to speak or understand Dutch, the concomitant use of melatonin and prior participation in this study.

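### Patients already delirious can enter this prevention trial, and the plan leaves unclear whether they count in the primary test, when that status is fixed, and whether the assumed 50% and 37% include them

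*Protocol article*

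**What the plan says.** **Eligibility (Study population and recruitment).** "Exclusion criteria are the inability to speak or understand Dutch, the concomitant use of melatonin and prior participation in this study". Delirium at enrolment is not on this list. Enrolment may take place up to 24 hours after admission.

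**Purpose (Discussion).** The study is described as a prevention trial, and occurrence of delirium was chosen as the primary measure for that reason.

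**Endpoint (Power analysis).** "The primary endpoint is the occurrence of delirium during the first eight days after the start of study medication".

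**Analysis (Statistics).** "Data will be primarily analysed according to the intention-to-treat principle and secondarily compared by per protocol analysis". The primary test is a chi-square test on occurrence of delirium. After the tests for the secondary outcomes comes the sentence: "Outcomes for patients who had delirium at day one of the study will be calculated separately".

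**Sample size (Power analysis).** The calculation is made "with a 50% incidence of delirium in the control group and an incidence of 37% in the intervention group", with "power of 80% and a two-sided alpha of 0.05", and arrives at 226 per group, 452 in total. The section does not say whether either rate includes delirium already present on day one.

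**Timing (Abstract; Data collection).** Study medication is given at 21:00 on five consecutive days. Visits are described from inclusion onwards, daily but only once during a weekend. No assessment before the first dose is described.

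**The concern.** The separate-calculation sentence shows that the authors expect some patients to be delirious on day one. Delirium present before the first dose cannot be prevented by that dose, so what happens to these patients affects the primary result. Two analysts could read the Statistics section in good faith and test different things:

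- **Kept in:** every randomised patient is analysed, and day-one cases are events in both arms. The observed difference is diluted, and a null result could partly reflect that dilution.
- **Taken out and reported apart:** fewer than 226 per arm remain, and the event rate among them may not be 50%.

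The second route has a further problem. If day one can include the hours after the 21:00 dose, a patient may be set apart because of an outcome that treatment could have influenced. The groups that remain are then no longer protected by randomisation.

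The sample size does not settle the matter, because it does not say which population its two rates describe.

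**Working it through.** **Inputs from the documents.** Control rate 0.50, melatonin rate 0.37, two-sided alpha 0.05, power 80%, 226 per arm (Power analysis). Absolute reduction 0.13; relative reduction 0.13/0.50 = 26%; risk ratio 0.74.

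**Assumed input.** The share q of patients delirious on day one is not given. I use 5%, 10% and 20%.

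**Formula.** Power = Φ{ [ |p1 − p2|√n − 1.96√(2p̄(1 − p̄)) ] / √(p1(1 − p1) + p2(1 − p2)) }, where p̄ is the mean of the two rates and n is the number per arm.

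**Step 1: the plan's own figure.** With pooled variance the required size is 228 per arm; with unpooled variance it is 225. The stated 226 is reproduced. At n = 226: 0.13 × √226 = 1.954; 1.96 × √(2 × 0.435 × 0.565) = 1.374; denominator √(0.25 + 0.2331) = 0.695. Power = Φ(0.835) = 79.8%.

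**Step 2: everyone analysed, 50% and 37% are whole-arm rates.** Power stays at 79.8% for any q. If day-one cases cannot be prevented, the whole 13-point reduction must come from the 0.50 − q of control patients who become delirious later. The relative reduction needed is 0.13/(0.50 − q):

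- q = 5%: 0.13/0.45 = 28.9%
- q = 10%: 0.13/0.40 = 32.5%
- q = 20%: 0.13/0.30 = 43.3%

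**Step 3: everyone analysed, the 50% includes day-one cases, and the 26% reduction acts only on the rest.** The melatonin rate becomes 0.50 − 0.26 × (0.50 − q). At q = 10% this is 0.396, and power = Φ((1.563 − 1.378)/0.699) = Φ(0.265) = 60.4%.

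**Step 4: day-one cases removed, 50% versus 37% in the rest.** Here n = 226(1 − q). At q = 10%, n = 203.4, and power = Φ((1.854 − 1.374)/0.695) = 75.5%.

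**Step 5: two intermediate readings.**

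- Removed, where the 50% had included them: control risk (0.50 − q)/(1 − q), multiplied by 0.74 for melatonin, with n = 226(1 − q).
- Everyone analysed, with day-one cases added as events to 50% versus 37% in the rest: q + (1 − q) × 0.50 against q + (1 − q) × 0.37, with n = 226.

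| Reading | q = 5% | q = 10% | q = 20% |
|---|---|---|---|
| All analysed, whole-arm rates (Step 2) | 79.8% | 79.8% | 79.8% |
| All analysed, 50% includes day-one cases, 26% in the rest (Step 3) | 70.8% | 60.4% | 38.3% |
| Removed, 50% v 37% in the rest (Step 4) | 77.7% | 75.5% | 70.5% |
| Removed, 50% had included them (Step 5) | 73.8% | 66.9% | 50.7% |
| All analysed, day-one cases added to 50% v 37% (Step 5) | 75.1% | 70.2% | 60.4% |

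**The case against.** The strongest defence is that the plan names one primary principle, intention to treat, and quotes its rates for the control group and the intervention group as wholes. On that plain reading everyone is analysed and power is 79.8% whatever the day-one share. This stands. A reader might infer that no reading delivers the planned power, and that would be wrong. What the plain reading leaves unsaid is that patients still at risk must then show a reduction larger than 26%.

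A reader might also infer that the Statistics section contradicts itself. It does not. The sentence says calculated separately, not excluded, and a separate subgroup report can sit beside an all-randomised primary analysis. The text is ambiguous, and nothing states that anyone is moved out of the comparison.

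Third, the power losses depend on an assumed share and an assumed mechanism. At 5%, removing day-one cases costs only about 2 points (77.7%). The Background section gives 53% for the group's earlier cohort. If that were the risk in at-risk controls, with the ratio 0.74 and 10% removed, power would again be 79.8%. This also stands, and the table shows a range, not a forecast.

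Finally, analysis-set definitions, the timing of the baseline assessment and a general allowance for losses are often left to a full protocol or analysis plan. I therefore make no point about other losses. The day-one rule is different: the article itself states it, in a form that leaves the primary comparison open. Consent by a legal representative is tied to cognitive impairment and is not evidence that delirious patients are enrolled. The eligibility list and the day-one sentence carry the point without it.

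**Conclusion.** The point holds as an ambiguity with consequences for the primary result. Patients already delirious can be randomised, the plan expects some, and it does not say whether they are events in the primary chi-square test. Nor does it place day one before the first dose or say which population the 50% and 37% describe.

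The arithmetic behind 226 per arm is sound. The cost of the ambiguity is either a larger effect needed in at-risk patients (28.9% to 43.3% instead of 26%) or power below 80%. With everyone analysed and the 50% including day-one cases, power is 70.8% to 38.3%. With day-one cases removed and 50% versus 37% in the rest, it is 77.7% to 70.5%. All of these ranges assume a day-one share of 5% to 20%, and the power figures also assume that the 26% reduction acts only on patients not yet delirious. The documents support neither a particular share nor a particular power loss. The risk of bias from separating patients on a post-dose status does not depend on these figures, but it arises only if day one is applied in that way.

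**What to change.** Before unblinding:

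1. Define the primary comparison as incident delirium, by assigned arm, in all randomised patients not delirious at the last assessment or clinical record before the first dose. Blinded treatment cannot have influenced that status, so the randomised comparison is preserved.
2. Report the all-randomised analysis as a sensitivity analysis, and describe patients delirious before the first dose without a formal test.
3. State that no patient is separated on a status observed after the first dose.
4. In the Power analysis section, say which population the 50% and 37% describe. Restate the power for the expected number at risk, using the blinded pooled share delirious before the first dose and the blinded pooled event rate.

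**Cost.** This is mainly wording, and no extra patients are required. The stated power will probably be lower, and the change clarifies the question without recovering lost power. It also moves the all-randomised analysis from primary to sensitivity in a trial already under way, so it must be documented as a blinded change. An assessment before the first dose cannot be taken for granted. For patients already enrolled, the status may have to come from admission records. Where none is available, those patients should stay in the primary set, at the price of some dilution.

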#### Secondary outcome measures

2] Severity and duration of delirium.

3] Subtypes of delirium.

4] Length of hospital stay.

5] Additional use of benzodiazepines during delirium.

6] Total dose of haloperidol for the treatment of delirium.

7] In-hospital complications.

8] Cognitive and functional decline twelve months after hospital admission.

9] Mortality during hospital stay and twelve months after hospital admission.

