### Study design

This study is a randomised, placebo-controlled, double blind, national, multicentre study with a one-year prospective follow-up. Figure 1 shows the design of the study. Informed consent is obtained from all patients or a legal representative in the case of cognitive impairment. Over five evenings, the patients receive the study medication consisting of a tablet containing either a placebo or 3 mg melatonin. Subsequently, daily assessment for the presence of delirium is performed, and the patients are followed for another three days. In total, each patient is observed for a minimum of eight days. For patients who are not delirious on day eight, daily assessments are stopped. For patients who are delirious by day eight, to evaluate duration of delirium, daily clinical assessments are continued until the symptoms of delirium are resolved or until the patient is discharged. Possible confounding factors including demography, fracture characteristics, type of anaesthesia, type of surgery and peri- and postoperative complications are registered for all patients. This study is carried out in compliance with the Helsinki Declaration. The Medical Ethics Committee (METC) of the Academic Medical Centre (AMC) has approved the study design, protocol and informed consent procedures. The executive board of Tergooihospitals has provided local feasibility approval.

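### Logistic regression is the only adjusted model named for the secondary outcomes, but several of them are not binary as measured

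*Protocol article*

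**What the plan says.** The Statistics section first assigns unadjusted tests by data type. For continuous measures: "Continuous secondary outcome measures, if normally distributed, will be tested using a Students' t-test, otherwise Mann-Whitney tests will be employed". For duration: "The duration of delirium will be tested using a log-rank test". Categorical outcomes get a chi-square test. As a later step, "multivariable logistic regression will be used to compare differences between melatonin and placebo groups in the primary and in the secondary outcome measures". That sentence is not limited to binary outcomes, and the article names no linear, Cox, ordinal or multinomial model.

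The list of secondary outcome measures includes "Severity and duration of delirium", "Length of hospital stay" and "Total dose of haloperidol for the treatment of delirium", as well as subtype, benzodiazepine use, complications, cognitive and functional decline, and mortality. Data collection fixes the scale of severity: "The severity of delirium is expressed as the maximum DRS-R-98 score during the delirium period". Study design fixes how duration is observed in patients still delirious on day eight: "daily clinical assessments are continued until the symptoms of delirium are resolved or until the patient is discharged".

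**The concern.** Logistic regression in its ordinary form takes a yes/no outcome. The paragraph recognises that some secondary outcomes are continuous and one is a time to an event, then gives all of them a model that fits neither type. This is a method that the article states, not a detail that it leaves to a fuller document. An analysis plan that followed the sentence would inherit the misfit, and one that departed from it would contradict the published design.

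Three things are at stake in the adjusted secondary analyses:

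- Each score, dose or time would have to be cut at a threshold that the article does not state, so the threshold could be chosen after the data are seen.
- For delirium duration, a yes/no version discards when the delirium resolved and does not deal properly with patients discharged while still delirious.
- An adjusted odds ratio for exceeding a cut-point is a different quantity from a difference in means, a shift in ranks or a comparison of resolution times. It therefore cannot show what adjustment does to the unadjusted result beside it.

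**Working it through.** **Step 1: the plan's own figure.** Inputs from Power analysis: 50% against 37%, power 80%, two-sided alpha 0.05. With unpooled variance, n per group = (0.50×0.50 + 0.37×0.63) × (1.960 + 0.842)² / 0.13² = 0.4831 × 7.849 / 0.0169 ≈ 224.4, so 225. The pooled-variance form gives 228. Power at 226 per group is 79.8%. The stated 226 reproduces, and the sample size is not in question.

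**Step 2: outcome types.** Splitting the eight numbered secondary items gives 11 endpoints.

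| Endpoint | Type as measured | Binary? |
|---|---|---|
| Severity | maximum DRS-R-98 score | no |
| Duration | time to resolution, observation ending at discharge | no |
| Subtype | categories (Delirium treatment mentions hyperactive and mixed) | no |
| Length of stay | time | no |
| Haloperidol | total dose | no |
| Cognitive decline | MMSE, IQCODE-sf | no, as measured |
| Functional decline | Katz count, grip strength | no, as measured |
| Benzodiazepine use | use or amount, not stated | unclear |
| Complications | any or number, not stated | unclear |
| In-hospital mortality | yes/no | yes |
| Twelve-month mortality | yes/no | yes |

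Seven of the 11 are not binary as measured. If cognitive and functional decline were each defined as yes/no, five would remain. The only scale cut-off in the article, an IQCODE-sf mean of 3.9, classifies impairment before admission. It is not a cut-off for an outcome.

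**Step 3: number of patients.** Severity, duration, subtype and the dose given to treat delirium arise only in delirious patients. Under the Power analysis rates: 226 × 0.50 = 113 and 226 × 0.37 = 83.6, about 197 in total. The twelve-month scales also rest on fewer than 452 patients, because those who have died cannot be assessed.

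**Step 4: illustration of the loss from cutting.** The article gives no standard deviations or cut-points, so a normal outcome is assumed. If a proportion q lies below the cut c, the information kept is φ(c)² / [q(1−q)], where φ is the standard normal density.

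- 50/50 split: 2/π = 0.637
- 70/30: 0.576
- 80/20: 0.490
- 90/10: 0.342

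In terms of power, take the standardised difference that a comparison of means detects with 80% power.

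- At 226 per arm: d = 2.802 × √(2/226) = 0.264. Cutting midway between the two means gives Φ(0.132) = 0.552 against 0.448, and power of about 61%.
- At 98 per arm, roughly half of 197: d = 2.802 × √(2/98) = 0.400. The proportions are 0.579 against 0.421, and power is about 60%.

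**The case against.** The strongest reply is that this is a condensed article and the sentence is loosely worded. The authors may have meant logistic regression only where the outcome is binary, with other models set out in the full protocol or analysis plan. The article never mentions dichotomising, the test named for duration is the log-rank test, and the regression comes only afterwards. This limits the point: the cut-points follow from reading the sentence literally and are not something the article announces. It does not remove the point, because the sentence names its scope and makes no exception.

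A second reply is that the logistic family is wider than the binary model. A proportional-odds model could take scores and a multinomial logistic model could take subtype, without cutting either. That is correct, so a reader should not infer that no logistic model could handle these outcomes intact. Neither extension is named, however, and neither deals directly with duration censored at discharge.

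A third reply concerns size. A reader might multiply the 36% loss by the full trial and conclude that 452 × 0.363 ≈ 164 patients are in effect thrown away. The documents do not support that. Several of these outcomes exist only in delirious patients, and times and doses cannot be assumed normal; the plan itself allows for Mann-Whitney tests.

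**Conclusion.** The point stands, limited to the adjusted analyses of the secondary outcomes. The one adjusted model named does not fit severity, duration, subtype, length of stay or haloperidol dose, nor the scales behind cognitive and functional decline unless decline is defined as yes/no. A reader might infer that the trial's main result is at risk. It is not: delirium occurrence and mortality are binary and suit logistic regression, and the unadjusted secondary tests fit their data types.

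The size cannot be fixed from the article. The 64% figure, and the fall from 80% to about 60% power, assume a normal outcome and a central cut. Uneven cuts keep less. The figure of 197 delirious patients assumes that the planning rates hold. The main weakness is qualitative: undefined thresholds, loss of timing and censoring for duration, and adjusted results that do not correspond to the unadjusted ones.

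**What to change.** Restrict logistic regression to binary outcomes: delirium occurrence, mortality, and complications or drug use if recorded as yes/no. For the rest, name a model by data type:

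- **Cognitive and functional scales:** linear or ordinal regression, adjusted for the admission value where one was collected. Data collection lists Katz, IQCODE-sf and grip strength. It lists no admission MMSE, although the Abstract speaks generally of comparison with admission, so adjust for baseline MMSE only if that value exists.
- **Delirium duration and length of stay:** Cox regression, stating how in-hospital death is handled.
- **Severity and dose:** ordinal or rank-based regression.
- **Subtype:** multinomial regression.

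If any scale is to be dichotomised, state the cut-point before unblinding. The change costs about a paragraph of text and some additional model fitting. It needs no new data, since baseline adjustment applies only to values already collected.
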